**Figure S3: Flow of study participant (incomplete)**

1. **Description of group characteristics at baseline**

For continuous variables, we will visually inspect histograms to assess whether they are normally distributed within intervention groups, with log-transformation of variables with a lognormal distribution. Population characteristics (Table 1) will be reported by intervention group as proportions, means (SD), geometric mean (geometric SD), and median (25th- and 75th percentiles) as appropriate, with corresponding group size. We will not test for group differences for reasons given by Assmann et al. [13].

Table S1: Description of baseline characteristics

| Variable | Type | Units/categories |
| --- | --- | --- |
| Age | Continuous | months |
| Age class | Binary | 12-23 months, 24-36 months |
| Sex | Binary | %males : %females |
| Height-for-age z-score | Continuous | SD |
| Weight-for-height z-score | Continuous | SD |
| Weight-for-age z-score | Continuous | SD |
| Haemoglobin concentration | Continuous | g/L |
| Anaemia status | Ordinal | *Severe to moderate anaemia:* haemoglobin concentration <89g/L; *mild anaemia:* haemoglobin concentration 90-109g/L; *non-anaemic:* haemoglobin concentration ≥110g/L |
| Plasma ferritin concentration | Continuous | μg/L |
| Iron status | Nominal | *Deficient:* plasma ferritin concentration <12 µg/L regardless of presence or absence of infection or inflammation; *replete:* plasma ferritin concentration ≥12 µg/L in the absence of infection or inflammation; *uncertain:* plasma ferritin concentration ≥12 µg/L in the presence of infection or inflammation |
| Plasma soluble transferrin receptor concentration | Continuous | mg/L |
| Plasma C-reactive protein concentration | Continuous | mg/L |
| Plasma *α*_1_-acid glycoprotein concentration | Continuous | mg/L |
| Inflammation | Binary | Plasma concentrations of C -reactive protein (CRP) > 5mg/L and/or α_1_-acid glycoprotein (AGP) > 1g/L |
| Whole blood ZPP concentration | Continuous | μmol/mol haem |
| Erythrocyte ZPP concentration | Continuous | μmol/mol haem |
| *Plasmodium* parasite density (asexual and sexual forms) | Continuous | µL^-1^ |
| *Plasmodium* infection, by rapid dipstick tests | Nominal | No infection; *P. falciparum* (by HRP2 or *P. falciparum*-specific pLDH), other human *Plasmodium* spp. (by pLDH), mixed infection |
| Urinary hepcidin concentration * | Continuous | nmol/mmol creatinine |
| Plasma folate concentration * | Continuous | nmol/L |

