| Plasma vitamin B_12_ concentration | Continuous | pmol/L |

* Funds permitting

1. **General issues in the analysis of intervention effects**

Effects are measured by comparing outcomes measured after a particular intervention with those measured if an alternative intervention has been given (counterfactual argument), thus focusing on comparison of end points (instead of before-after measurements within groups). We will estimate effects when possible; P-values, where reported, will be 2-sided. We will avoid hypothesis testing and interpretation of results as ‘significant’ or p<0.05 for reasons reported elsewhere [14,15].

We will describe outcome variables by intervention groups as proportions, means (SD), geometric means (geometric SD), and median (25^th^- and 75^th^ percentiles) as appropriate, with corresponding group sizes. For continuous outcomes, these estimates will be obtained by ANOVA.

Intervention effects will be assessed as absolute differences (proportions and means) or relative differences in geometric means (variables with lognormal distributions) between groups, with accounting for the stratified block design. To facilitate interpretation, odds ratios resulting from these analyses will be converted to differences in proportions. To allow extrapolation of results to other settings, we will also consider reporting relative effects for binary outcomes (i.e. proportion ratios). Outcomes that are not normally distributed, even after log-transformation, will be compared using non-parametric tests (e.g. Mann-Whitney U test, or Wilcoxon rank sum statistics)

1. **Analysis of the primary outcome (objective 1a and 2)**

*Primary analysis:* We will estimate the difference in haemoglobin concentrations at the end of the 30-day fortification period between groups of children allocated to different iron formulations. Non-inferiority will be rejected if the difference between groups is less than the non-inferiority margin.

*Secondary analysis* of the primary outcome will be as follows:

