Categorisation of baseline factors has the advantage that results can be conveniently presented in a forest plot. It has the disadvantage, however, that the precision of the interaction depends on the number and position of the cut-off values used to categorise baseline factors [16]. We will also explore interactions with baseline factors as continuous covariates, using fractional polynomials [16]. Such a strategy is more powerful, especially at towards extreme ends of the covariate distribution where limited numbers of observations generally preclude detection of interaction, and it may reveal more about the nature of possible interactions. We will inspect scattergrams and conduct sensitivity analysis as needed to examine the influence of possible outliers on results.

Results of subgroup analyses will be interpreted cautiously for reasons reported elsewhere [13].

1. *Intention-to-treat analysis:* For binary outcomes, pooled estimates from multiple iterations may result in non-integer values. This precludes computation of confidence intervals for differences in proportions, and may be counterintuitive to readers not well versed in multiple imputation techniques. To handle this problem, we will calculate differences in means under the assumption of binary outcome variables having a Bernoulli distribution. Pooled chi-squared statistics for cross-tabulated data and associated p-values will be calculated as described by Van Buuren (2012), thus the p-values obtained are only crude estimates of the true values [17].
2. *Paired comparisons of iron groups with placebo (objective 2):* This analysis will be done as for the comparison between iron groups (see above). Superiority will be established if no effect is excluded from the 95% CI.
3. **Analysis of secondary outcomes (objectives 1b and 2)**

To assess intervention effects, we will conduct all three possible paired comparisons between the intervention groups. We will use plasma ferritin concentration as an outcome indicator of iron status, and soluble transferrin receptor as an outcome indicator of the iron demand by the erythrocytes (both measured at the end of the 30-day intervention period). We will conduct analysis with and without adjustment for baseline factors, as well as intention-to-treat analysis (see methods above).

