Plasma ferritin concentration has the limitation that it can be enhanced by inflammation independently of iron status. Because our interest in plasma ferritin concentration is limited to its value as a marker of iron status, we will adjust all analysis for inflammation markers (plasma concentrations of C -reactive protein and α_1_-acid glycoprotein; both as continuous variables) measured at the end of the 30-day intervention period. Thus we will effectively measure effects on plasma ferritin concentration assuming no inflammation.

Similarly, plasma soluble transferrin receptor concentration can be elevated by an increased erythropoiesis under influence of malaria-induced haemolysis. Because our interest in plasma soluble transferrin receptor concentration is limited to its value as a marker of tissue iron demand, we will adjust all analysis for inflammation markers (plasma concentrations of C -reactive protein and α_1_-acid glycoprotein; both as continuous variables) measured at the end of the 30-day intervention period.

Stratified analysis will be used to measure effect sizes within subgroups. To assess effect modification directly, we will compare multiple logistic regression models with and without product terms, with categorical baseline factors entered as dummy-coded variables.

1. **Multiplicity**

Multiple comparisons to evaluate non-inferiority (section 6) or to measure effects on multiple secondary outcomes may raise concerns about multiplicity (i.e. occurrence of false-positive results). We consider statistical solutions (e.g. Bonferroni correction) to be inappropriate in our trial because a) the concept of multiplicity is rooted in hypothesis testing, which is not our framework for making inferences; b) we will not formally adjust for multiplicity because any absence or present effect differences will be interpreted by the confidence interval in the context of the set thresholds as defined in section 6 [14,15,12]; c) for an intervention that leads to multiple changes in related outcomes, results from multiple comparisons are mutually reinforcing, not mutually debasing [18] .

In case of substantial discordance in results from analyses to evaluate non-inferiority, we will consider the results to be indeterminate.

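### Effect modification for the secondary outcomes is to be assessed by logistic regression, but the only outcomes named, ferritin and sTfR, are continuous and no binary version is defined

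*SAP*

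**What the plan says.** In the SAP section on the analysis of secondary outcomes (objectives 1b and 2), the outcomes are set out in one sentence: "We will use plasma ferritin concentration as an outcome indicator of iron status, and soluble transferrin receptor as an outcome indicator" of erythrocyte iron demand, both taken at the end of the intervention period. No other outcome is named there.

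Table S1 lists both as continuous variables at baseline. The row for sTfR reads "Plasma soluble transferrin receptor concentration | Continuous | mg/L", and ferritin is typed the same way in μg/L.

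The section on general issues in the analysis of intervention effects sets the effect scale. Effects are absolute differences for means and proportions, or "relative differences in geometric means (variables with lognormal distributions) between groups". It also foresees odds ratios, to be converted to differences in proportions, without naming the outcomes that would give rise to them.

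The secondary-outcome section then adjusts ferritin for C-reactive protein (CRP) and α1-acid glycoprotein (AGP) as continuous variables and states the target: "Thus we will effectively measure effects on plasma ferritin concentration assuming no inflammation". The same adjustment is set for sTfR. The closing paragraph has stratified analysis give the effect sizes within subgroups and, for a direct assessment of effect modification, says "we will compare multiple logistic regression models with and without product terms, with categorical baseline factors entered as dummy-coded variables".

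For haemoglobin, the continuous primary outcome, the corresponding section uses multiple linear regression for covariate adjustment and a multiple regression model with multiplicative interaction terms for subgroups.

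**The concern.** Logistic regression needs a categorical outcome, in ordinary use a binary one. The section supplies two concentrations and no rule for turning either into a yes/no variable. An analyst who follows the sentence literally must choose a cut-off that the plan does not give. By its preamble, the plan was completed after data collection but before unblinding and overrides the trial proposal, so this is the document in which the choice should be fixed.

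Three things are at stake. The cut-off would be open to choice after the data are seen. Information would be lost in an interaction analysis, which is usually imprecise to begin with. And the product term would be a ratio of odds ratios, while the subgroup effects shown beside it would be mean differences or geometric-mean ratios. Interaction depends on scale: an odds-ratio interaction can appear or vanish only because the proportion below the cut differs between subgroups, so the model would not examine the effects on display.

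**Working it through.** The plan gives no figure on this point, so there is none to reproduce. The check has two parts.

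**1. Does the text supply a binary outcome?**

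- *Ferritin.* The threshold of 12 µg/L appears in Table S1, which describes baseline characteristics. The classification is nominal with three classes (deficient, replete, uncertain), so it is not binary without a further rule for the uncertain children. The plan does not carry it over to day 30.
- *sTfR.* The only cut is at the median. It is applied to the baseline value, to form subgroups in the primary-outcome section.
- *Other outcomes.* Objective 2 extends to the indicators of objective 1, which include *P. falciparum* infection, and presence of antigenaemia would be binary. The secondary-outcome section does not name it.

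No binary version of either named outcome is defined.

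**2. What would dichotomising cost?**

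For an outcome that is normal, or normal after log-transformation, the asymptotic information kept after one cut, relative to the continuous analysis, is φ(z_p)² / [p(1 − p)]. Here p is the share of children below the cut, z_p the matching normal quantile and φ the standard normal density. The sample-size penalty is the inverse. At the median, φ(0)² / 0.25 = 0.1592 / 0.25 = 0.637, and 1 / 0.637 = 1.57.

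| Share below the cut | Information kept | Lost | Sample-size penalty |
|---|---|---|---|
| 50% | 64% | 36% | 1.57 |
| 40% | 62% | 38% | 1.61 |
| 30% | 58% | 42% | 1.74 |
| 20% | 49% | 51% | 2.04 |
| 10% | 34% | 66% | 2.92 |
| 5% | 22% | 78% | 4.47 |

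The median is the best case. The share kept falls to one half at p ≈ 0.21 and, by symmetry, at p ≈ 0.79. With the target of 108 per group, a median split is worth about 108 × 0.637 ≈ 69 per group analysed as continuous.

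A simulation shows the effect on an interaction analysis. It had two arms of 108, a binary modifier with equal probability, normal errors with SD 1, a treatment effect of 0.2 SD, a modifier effect of −0.2 SD, an interaction of 0.8 SD and 1,500 runs. All the effect sizes are assumptions. The interaction was chosen so that the linear model has power a little above 80%. Tests were two-sided at 5%: the product term in the linear model, and the likelihood-ratio comparison of logistic models with and without it.

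| Cut (share below) | Linear model | Logistic model |
|---|---|---|
| 50% | 84% | 63% |
| 30% | 83% | 58% |
| 20% | 82% | 51% |
| 10% | 85% | 38% |

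The linear column does not depend on the cut; its variation is simulation error. At the 20% and 10% cuts, 1 and 12 runs gave no logistic fit and were left out of the logistic column.

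**The case against.** The strongest reply is that nobody was going to dichotomise ferritin. The sentence itself names neither ferritin nor sTfR. The section heading includes objective 2, which reaches *P. falciparum* infection; that outcome is not among those the plan sets aside, and odds ratios and binary outcomes are discussed elsewhere. Or the word is simply a slip for linear, since haemoglobin is handled by linear regression. If a cut were wanted, objective 1b concerns iron status and 12 µg/L is the obvious candidate. The matter also touches only effect modification of secondary outcomes, in a plan that avoids significance testing.

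Much of this stands. Either benign reading is plausible, and the information loss arises only if the sentence is followed literally for the two concentrations. But neither reading leaves the text correct. If it is meant for infection, ferritin and sTfR have no stated interaction model. If it is a slip, the stated method is wrong and conflicts with the approach to haemoglobin. The 12 µg/L threshold would still need a rule for the uncertain class, and it does nothing for sTfR.

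A reader might also infer more than the document supports:

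- *That most of the information would be lost.* The plan gives neither a day-30 cut-off nor an expected prevalence. A cut near the median keeps about 64%, and more than half is lost only beyond roughly the 21st or 79th percentile.
- *That all effects here are geometric-mean ratios.* That scale applies only if the variable proves lognormal.
- *That the interaction has four times the variance of the main effect.* That holds for equal-sized subgroups, and the subgroup sizes are not given.

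**Conclusion.** The point holds as an error in a stated analysis rule: the model named cannot be applied to the only outcomes named, and no definition in the plan makes it applicable. If it were followed by dichotomising, the loss would be at least about 36% of the information, assuming a normal or lognormal outcome and a single cut, and the interaction would be on a different scale from the subgroup effects. The simulated fall in power from about 82–85% to 63% at best illustrates this under assumed effect sizes; it is not a prediction for this trial.

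It should not be read as evidence that dichotomisation was intended. The primary haemoglobin comparison, the non-inferiority margin and decision, and the main effects on ferritin and sTfR are untouched. It is worth correcting because the error is plain and the correction is free.

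**What to change.** In the last paragraph of the secondary-outcome section:

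- Replace *logistic* by *linear*: multiple linear regression models of the day-30 concentration, log-transformed if lognormal as the plan already provides, compared with and without arm-by-factor product terms.
- Keep in these models the adjustment for the stratified design and for CRP and AGP that the plan already requires.
- Report the interaction on the scale of the stratified effects, with a 95% CI: a ratio of geometric-mean ratios for log-transformed outcomes, otherwise a difference in mean differences.
- Reserve logistic models for binary outcomes that are named and defined in the plan. If *P. falciparum* infection was the intended outcome of the sentence, say so.

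The cost is a sentence or two of wording. No new data, no change in sample size and no change to the primary analysis are needed.
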